### Healthy conversations @ playgroup intervention

The Healthy Conversations @ Playgroup program aims to address the underlying behavioral risk factors for obesity and chronic disease by helping parents take effective steps to improve their children’s dietary, physical activity, screen time, and sleep behaviors. Grounded in Social Cognitive Theory [23] and Self-Determination Theory [24], the intervention comprises 10 “healthy conversations”, led by a peer facilitator, designed to increase parents’ behavioral capability and self-efficacy to implement autonomy-supportive parenting practices related to healthy eating, physical activity, screen time, and sleep. The intervention utilizes Behavior Change Techniques to change parenting health behavior practices, as classified the Behavior Change Technique Taxonomy v1 [25]. Behavior change techniques include goal setting (behavior), problem solving, action planning, review behavior goal(s), social support (unspecified), instruction on how to perform a behavior, behavior substitution, and verbal persuasion about capability (Additional file 1). The program will be delivered biweekly, on-site during regularly scheduled playgroup sessions by trained peer facilitators over a 10-week period (which coincides with the Australian public-school term). Informed by the results of focus groups conducted in community playgroups [26], the intervention addresses five major themes, which are described in Table 3.

**Table 3 Tab3:** Description of the five healthy conversation topics and key messages

Healthy conversation topics	Key messages
***Session 1 – Reducing stress at mealtimes***	
Food refusal and child hunger/fullness	“Parent provides, child decides”: Parents can provide healthy meals and snacks; and let the child decide if they are hungry.
Supporting child taste development	Offering new or disliked foods multiple (10–12) times helps children taste and accept (or even like) new foods.
***Session 2 – Limiting screens without tantrums***	
Create a family digital media plan	Creating a ‘family technology plan’ helps everyone in your family balance and manage technology use.
Alternatives to screens	Limiting screen time is challenging so it helps to plan ahead and make a “toolbox” of alternatives.
***Session 3 – Supporting movement skills in children***	
Get children moving with active play	For young children, physical activity is about active play. It does not have to involve structured or planned activities.
When it comes to encouraging active play, parents make a difference	Parents make a difference – encourage your child to be active by watching them, participating with them, and helping them discover activities they like to do.
***Session 4 – Bedtime activities and routines to support sleep***	
Creating a bedtime routine	A consistent bedtime routine can help children sleep.
Overcoming barriers to bedtime routines	Make the bedroom environment as “sleep friendly” as possible and enlist the support of “significant others” in implementing sleep routines.
***Session 5 – Celebrating achievements***	
Wins with food refusal and child taste development	Be confident in yourself and your ability as a parent to positively influence your child’s health behaviors.
Wins with screen time, active play, and sleep	Keep up the good work and be kind to yourself!

### What is a healthy conversation?

A healthy conversation takes place opportunistically between parents attending the regularly scheduled playgroup. With the guidance of a trained peer facilitator, parents are encouraged to share and reflect on parenting challenges related to healthy eating, screen time, physical activity, and sleep with a view towards making small but important changes to improve their child’s health. The conversation typically concludes with signposting to follow-up support services or information. Initially developed for use in health care settings [27], the healthy conversations approach has been successfully implemented in other settings. Most notably, this approach has been used by childcare workers in the United Kingdom to improve diet and physical activity in families experiencing socioeconomic disadvantage [28].

### Peer facilitators

The intervention will be delivered by trained peer facilitators. Peer facilitators will not be researchers or health professionals, but parents who have training and/or experience in communications and group facilitation. In our pilot study, this approach was shown to be more feasible than training a volunteer parent from each community playgroup [29]. Facilitator training will involve the equivalent of a full day face-to-face skills-based workshop (hybrid in-person and video link) and biweekly video link peer support meetings to check-in and assist with fidelity maintenance across the three sites. Through skill-based learning strategies, problem-solving and role-plays, peer facilitators will be taught how to: 1) deliver each component of the intervention; 2) effective facilitation skills; 3) identify and overcome common barriers to program implementation; and 4) use of social media for signposts. Prior to the workshop, peer facilitators will receive a Facilitator Handbook (hard copy and electronic) which provides a complete list of open-ended questions for conversation starters, suggestions for open-ended discovery questions and prompts, suggested responses to parent comments, suggestions for wrapping up the conversation and goal setting, and copies of the social media signpost.

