### Sample size and power

For Aim 1, the intervention effect is the net difference for change in the healthy lifestyle behaviors immediately post intervention and at 6-months follow-up. The research hypothesis is that the intervention will result in net differences of 0.5 serving of vegetables (38 g per day), 1.5 servings of discretionary foods per day, 15 min or 2% of time in MVPA, 30 min screen time per day, and 40 min of sleep per 24 h period. The null hypothesis is a net difference of zero. For Aim 2, the intervention effect is the net difference for change in BMI z-score at 6-months follow-up. The research hypothesis is that the intervention will result in a difference of 0.30 BMI z-score units. The null hypothesis is a net difference of zero. For a 2-year-old at the 84th percentile or a BMI z-score of 1.0, a difference of 0.30 z-score units equates to a clinically meaningful reduction of 0.4 kg in excess weight.

Table 2 reports minimal detectable differences for samples of 20, 30, and 40 community playgroups per condition. All calculations were performed assuming a power of 0.80, a 2-tailed alpha level of 0.05, an average cluster size of six parent-child dyads, and an intra-cluster correlation (ICC) of 0.10 and 0.02 for the child health behaviors and BMI z-score, respectively. Standard deviation estimates for vegetable intake were based on dietary intake data from the NOURISH randomized controlled trial [20]. The standard deviations for time in physical activity and screen time were based on previously published studies in Australian children aged 0–5 years [21]. The standard deviation for sleep duration was based on published data on Australian children [10]. The standard deviation for change in BMI z-score was based on data from the NOURISH randomized controlled trial [20]. Based on these calculations, a sample of 30 playgroups per condition achieves ≥80% power to detect the hypothesized between-group differences for each of the primary outcomes. To offset a projected attrition rate of up to 25%, an additional two children within each playgroup will be recruited, providing an overall sample of 60 community playgroups and 480 parent-child dyads.

**Table 2 Tab2:** Minimal detectable differences for child health behaviors and BMI z-score

Study Outcome	Hypothesised Effect	Est. SD	20 Playgroups (***n*** = 120)	30 Playgroups (***n*** = 180)	40 Playgroups (***n*** = 240)
Veg Intake	½ serve, 38 g/d	58 g/d	26 g/d	21 g/d	18 g/d

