### Wait-list control

The intervention playgroups will be compared to a wait-list control group completing their usual playgroup sessions. Playgroups allocated to the wait-list control group will be offered the 10-week program at the conclusion of the 6-month follow-up assessment.

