### Statistical analysis

Statistical analyses will follow standard principles for RCTs using two group comparisons including all participants on an intention-to-treat basis. Between-group differences in the primary and secondary outcomes will be tested using a general linear mixed model, which accounts for the clustering of parent-child dyads within playgroups. Within each model, condition, time, the condition by time interaction will be included as fixed effects, with playgroup nested within condition, parent-child dyads nested within playgroup and condition, and the playgroup by time interaction nested within condition included as random effects.

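### If peer facilitators each lead several intervention playgroups, the planned model omits clustering that exists in one arm only, so its standard errors are too small and the stated power carries an unstated assumption

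*Protocol article*

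**What the plan says.** Under Peer facilitators, the protocol article says that the sessions are led by parents with training or experience in communication and group facilitation, and gives the reason: "In our pilot study, this approach was shown to be more feasible than training a volunteer parent from each community playgroup". It does not say how many facilitators there are or how many playgroups each leads. Under Wait-list control, the intervention playgroups are "compared to a wait-list control group completing their usual playgroup sessions"; the programme is offered to them only after the 6-month follow-up.

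Under Statistical analysis, the mixed model "accounts for the clustering of parent-child dyads within playgroups". The random effects are listed in full: playgroup within condition, dyad within playgroup, and playgroup by time. None is for facilitator.

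Under Sample size and power, the only clustering input is "an intra-cluster correlation (ICC) of 0.10 and 0.02 for the child health behaviors and BMI z-score, respectively", and the conclusion is that "a sample of 30 playgroups per condition achieves ≥80% power to detect the hypothesized between-group differences for each of the primary outcomes".

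**The concern.** Playgroups led by the same person share that person's skill and fidelity to the programme. If this affects outcomes, their results are correlated. Control playgroups have no such link. Both the model and the power calculation treat the 30 intervention playgroups as independent, so a variance component that can exist in one arm is left out of the error term.

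At stake are confidence intervals that are too narrow for the treatment comparison on every primary outcome, and a power statement that holds only without facilitator clustering. The Discussion part of the abstract names scale-up across Australia as the intended use. That means delivery by other facilitators, so variation between facilitators matters to the inference the trial wants to make.

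**Working it through.** **Inputs from Sample size and power and Table 2.** "a power of 0.80, a 2-tailed alpha level of 0.05"; "an average cluster size of six parent-child dyads"; 30 playgroups and 180 dyads per arm; playgroup ICC 0.10 (behaviours) or 0.02 (BMI z-score); the hypothesised effects and SDs in Table 2. The six dyads are those left after attrition: "To offset a projected attrition rate of up to 25%, an additional two children within each playgroup will be recruited", and 360/(1 − 0.25) = 480.

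**Inputs that are assumptions.** The number of facilitators K (3, 6, 10, 15) and the facilitator ICC ρ (0.01, 0.02). The article gives neither.

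**Step 1: reproduce the plan.** In SD units, the variance of the arm difference is V0 = 2(1 + 5·ICC)/180. This is 0.01667 for behaviours and 0.01222 for BMI z-score. The minimal detectable difference is (1.96 + 0.84)·SD·√V0, which gives 21.0 g/d, 0.72 serv/d, 1.81%, 27.1 min, 34.7 min and 0.279 z. Table 2 has 21, 0.7, 1.8, 27, 35 and 0.28, so it reproduces. Power at the hypothesised effects is 99.9% (vegetables), over 99.9% (discretionary foods), 87.2% (physical activity and screen time), 89.7% (sleep) and 85.4% (BMI z-score).

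**Step 2: add facilitators to the intervention arm.** The true variance becomes V = V0 + ρ/K. A model with playgroup as the top level sees only V0 + ρ·[1 − (30/K − 1)/29]/30. Type I error is 2·[1 − Φ(1.96/r)], where r is the square root of the ratio of these two variances.

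Example, BMI z-score, K = 6, ρ = 0.02: V = 0.01222 + 0.00333 = 0.01556. The model sees 0.01222 + 0.02·(1 − 4/29)/30 = 0.01280. So r = √(0.01556/0.01280) = 1.10, and the error is 7.5%.

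| K | ρ | Error, behaviours | Error, BMI z |
|---|---|---|---|
| 3 | 0.01 | 7.2% | 8.0% |
| 3 | 0.02 | 9.3% | 10.8% |
| 6 | 0.01 | 5.9% | 6.3% |
| 6 | 0.02 | 6.9% | 7.5% |
| 10 | 0.02 | 5.9% | 6.3% |
| 15 | 0.02 | 5.5% | 5.6% |

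Simulating playgroup means (100,000 runs per row, t-test) agrees to within about 0.3 percentage points.

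**Step 3: power at the hypothesised effects, with the correct variance.** Power = Φ(effect/(SD·√V) − 1.96). The second figure in each cell uses a t reference with Satterthwaite degrees of freedom (K − 1 for the intervention arm, 29 for control).

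| K | ρ | Physical activity, screen | Sleep | BMI z |
|---|---|---|---|---|
| 3 | 0.01 | 81% / 65% | 84% / 68% | 76% / 59% |
| 3 | 0.02 | 75% / 55% | 78% / 58% | 68% / 47% |
| 6 | 0.01 | 84% / 79% | 87% / 82% | 81% / 75% |
| 6 | 0.02 | 81% / 75% | 84% / 78% | 76% / 69% |
| 10 | 0.02 | 83% / 80% | 86% / 83% | 80% / 76% |
| 15 | 0.02 | 85% / 83% | 87% / 86% | 82% / 80% |

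Vegetables and discretionary foods stay at 99% or more by normal approximation throughout. With the t reference their lowest values are 92% and 97%, at K = 3 and ρ = 0.02.

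**Step 4: detectable differences.** They grow by √(V/V0). At K = 6 the BMI z-score figure goes from 0.279 to 0.297 (ρ = 0.01) or 0.314 (ρ = 0.02), against a hypothesised 0.30.

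**Sensitivity.** These figures add facilitator variance on top of the stated playgroup ICC. If the total within-playgroup ICC is held at the stated value instead, BMI z-score power at K = 6 is 82% (ρ = 0.01) or 78% (ρ = 0.02) by normal approximation. All figures refer to a single follow-up time, as Table 2 does.

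**The case against.** The strongest reply is that the article nowhere says facilitators are few or that each leads several playgroups. A reader might infer this from the preference for trained facilitators over a volunteer from each playgroup. The inference is reasonable, but it remains an inference. With one facilitator per playgroup, the playgroup terms would absorb the effect; with 15, the error stays close to 5%. This stands, and makes the point conditional.

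A reader might also conclude that the stated 80% power is simply wrong. The documents do not support that. Power at the Table 2 detectable differences is 80% by construction, so any added variance pushes it below 80%. The article's claim is about the hypothesised effects, where power starts at 85% or more. Two outcomes are safe in practice, and the others fall short only under some combinations of K and ρ.

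Nor is the inflation of type I error unconditional. If the programme has no effect under any facilitator, there is no facilitator variance from delivery. Inflation needs an average effect of zero with real differences between facilitators, which means inference to facilitators beyond those in the trial. The shared handbook, common training and biweekly support meetings may also keep ρ small. For BMI z-score, ρ = 0.02 equals the whole assumed playgroup ICC and should be read as the upper end of the range.

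Finally, a separate analysis plan may deal with this. The random effects and the power basis, however, are fixed in the article, and neither includes facilitators.

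**Conclusion.** The point holds conditionally. If facilitators are shared across intervention playgroups and differ in effect, the planned model gives standard errors that are too small for every primary outcome, and the Table 2 detectable differences are optimistic. For assumed facilitator ICCs of 0.01 to 0.02, the inflation is modest with 6 facilitators, material with 3 and negligible with 15.

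The power claim has slack. BMI z-score, the only Aim 2 outcome, is the most exposed. Physical activity, screen time and sleep can fall below 80% when facilitators are few. Every size given here rests on an assumed number of facilitators and an assumed facilitator ICC.

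**What to change.** 1. State the number of facilitators and the playgroups each leads, and record facilitator ID on the checklist already completed after each session. If each playgroup has its own facilitator, saying so settles the matter.
2. Where facilitators lead more than one playgroup, add to the model a facilitator random effect in the intervention arm only, at the post-baseline times (a partially nested model), with small-sample degrees of freedom. If there are too few facilitators to estimate the variance, report this as a sensitivity analysis.
3. Under Sample size and power, say that the 80% figure assumes no facilitator clustering. Give power at the hypothesised effects over a range of facilitator numbers and ICCs.

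The cost is one variable, one model term and a short table, with no extra participants. Intervals become wider, appreciably so with very few facilitators, and the stated power becomes less favourable. The Facebook groups, one per site, are a further link between intervention playgroups, at site level. The facilitator term does not capture it.

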### Implementing healthy conversations at playgroup

During each program session, the peer facilitator will lead two 10- to 15-min healthy conversations related to a specific theme. The facilitator opens the discussion with a question for the group (conversation starter) and then guides the discussion using open-ended questions and prompts. Parents are encouraged to reflect on what they currently do as parents – the actions, behaviors and strategies they use to encourage, discourage, support, or manage their child’s health behaviors. Parents are encouraged to think about “what works” for them and “what they could do differently” to improve health behaviors. Through group discussion, parents collectively formulate ideas and strategies to deal with specific challenges. When necessary, the facilitator provides ideas to keep the conversation moving and on track. At the end of the discussion, the facilitator encourages parents to select a clear and achievable strategy from those discussed in the conversation to implement at home.

### Signposting intervention

Between each session, parents will receive ‘signposts’ directing them to information and support about the topics covered. These signposts will be delivered via social media, using private Facebook groups set up for the purpose of the program (one per site to align with differing school term dates between sites). Project staff will post content to the Facebook group two times between each session. Each post will be related to the most recent conversation topics, and may include videos, links to articles and prompts to action. The aim is to provide participants with further information on the topic, prompt action in relation to the health behavior discussed at the previous session, encourage sharing of experiences, and increase social support. Facilitators will moderate posts (e.g., remove posts, pin, or unpin posts) and respond to comments posted by parents.

### Wait-list control

The intervention playgroups will be compared to a wait-list control group completing their usual playgroup sessions. Playgroups allocated to the wait-list control group will be offered the 10-week program at the conclusion of the 6-month follow-up assessment.

### Participant characteristics

Demographic information will be collected at baseline using an online survey and will include child date of birth, child sex, parental age, parental education, and family structure.

### Primary outcomes

#### Dietary intake

Children’s dietary intake will be reported by parents using a short questionnaire developed to assess obesity-related dietary behaviors in 1- to 5-year-olds [30]. The 13-item questionnaire asks parents to report how many times over the past 7 days their child has consumed vegetables (2 items), sweetened drinks (e.g., fruit juice, cordial/squash, soft drinks/soda, flavoured milk; 2 items) and discretionary foods (e.g., chocolate, potato crisps or savory biscuits, processed meat, sweet baked goods, takeaway foods; 7 items), as well as type of milk (1 item) and bread (1 item) consumed. The short dietary questionnaire has been shown to have acceptable relative validity (Spearman’s rho = 0.62 to 0.89) and test-retest reliability (ICC = 0.80–0.97) [30].

#### Physical activity

The percentage of daily time spent in moderate-to-vigorous intensity physical activity (MVPA) will be measured using the Axivity AX3 accelerometer (Axivity Ltd. Newcastle, United Kingdom). Participants will receive the accelerometer and an information pack via express mail. The pack will include an introductory letter to parents, a detailed instruction sheet, an activity monitoring log sheet to record any activity monitor removals, and a pre-paid padded envelope to return the accelerometer and log sheet to the research team. The child will be asked to wear the accelerometer on their non-dominant wrist 24-h per day for seven consecutive days (except for bathing or water-based activities).

Upon return of the accelerometer via express mail, raw accelerometer data (50 Hz) will be downloaded and processed into physical activity metrics using a random forest physical activity classification algorithm specifically developed for children under five [31]. This validated machine learning algorithm uses 20 features extracted from the raw tri-axial acceleration signal to classify activity type and quantify daily time spent in sedentary activities (sitting or lying down), light-intensity activities and games (slow walking, standing, standing arts and crafts), walking, running, and moderate-to-vigorous intensity activities and games (active games with balls, riding bikes/scooters). In a free-living evaluation, the random forest algorithm exhibited an overall classification accuracy of greater than 80%. MVPA will be calculated by summing daily time spent in walking, running, and moderate-to-vigorous activities and games.

#### Screen time

Children’s screen time will be measured using four items from the Movement Behaviour Questionnaire (MBQ). Parents will report the amount of time their child spends: watching television programs, videos/internet clips or movies on a television, computer, or portable/mobile device such as tablet or smartphone; and, playing games, looking at photos, or video chatting on a screen-based device such as a computer or laptop, videogame console, iPad, tablet, or smartphone. Responses will be recorded for a typical weekday and weekend day over the past week. To estimate sedentary screen time, parents will report the amount of time their child was using screens while standing or being active. Sedentary screen time will be calculated by subtracting “active” screen time from total screen time. Weekday and weekend responses will be averaged to estimate total screen time and sedentary screen time. The screen time estimates from the MBQ have been shown to exhibit excellent test-retest reliability (ICC = 0.91 to 0.93) [30].

#### Sleep

Sleep duration over the previous week will be parent reported using three items from the MBQ. These items assess typical day and night sleep duration and regularity of evening sleep routine. Sleep duration and regularity responses from the MBQ have been shown to exhibit excellent test-retest reliability (ICC 0.85–0.95) [30]. Sleep duration and quality will also be measured using data from the AX3 accelerometer. Raw acceleration signal from the wrist will be scored for sleep-wake state using the algorithm developed by Van Hees and colleagues [32].

